#### Economic analysis

Economic analysis of the cost-effectiveness of the intervention program will be conducted by a Health Economist. This will involve two distinct elements; firstly, a cost analysis of the physical activity and nutrition program which will provide estimates of the actual cost of the program and inferences into cost of future programs. The second aspect will include the undertaking of cost-effectiveness [35]. Quality of life will be measured using the validated EQ-5D-3 L questionnaire which is a standardised measure of health status developed by the EuroQol Group [32]. The self-complete EQ-5D-3 L questionnaire will be administered at baseline and post- test. This is a simple questionnaire which is cognitively undemanding, taking only a few minutes to complete. Sensitivity analysis will be undertaken to test the robustness of the results.

### Process evaluation

Process evaluation will assess: fidelity (quality); dose delivered (completeness); dose received (exposure, satisfaction); reach (participation rate); recruitment; and context (aspects of the environment influencing implementation or outcomes) of the intervention [36]. This will be conducted on the intervention group via a brief questionnaire administered by mail and/or internet. It will ask participants to evaluate the resources (readability, usefulness of advice, suitability and relevance to age group) based on procedures previously used by the research team [37]. Process evaluation is essential to identify the appropriateness of the intervention and research procedure.

A subgroup of the intervention participants (n = 20) will be randomly selected to take part in exit interviews. The sample size used is comparable to a previous study [13]. While the literature has identified that sample size recommendations for non-probabilistic, purposive qualitative studies can range from five to 25 participants, saturation usually occurs within the first 12 interviews [38]. Both program completers (n = 10) and non-completers (n = 10) will be contacted by telephone to gain their perceptions of the program and resources. The non-completers will be asked the reasons for withdrawal. Each interview is estimated to take between 20 and 30 minutes. Permission will be sought for recording the interviews.

### Statistical analysis

Comparisons between the changes in intervention and control groups will be performed using univariate and multivariable statistical methods. Outcome variables at baseline and post- intervention will be used to test the hypotheses in association with the covariates and confounding demographic and lifestyle variables. Continuous and categorical outcomes will be analysed using generalised linear mixed regression models, accounting for the correlations between repeated measures and clustering of the observations. Intention-to-treat analysis will be conducted to assess sensitivity of the results to the expected attrition and withdrawal of participants from the RCT.

All qualitative data will be transcribed within two weeks of interviewing. At least 10% of all data will be randomly selected and reviewed. Data will be coded and common themes or categories created. The information obtained will be collated, presented thematically and supported by direct quotes from participants. Data management of full transcripts and other text will be facilitated by NVIVO [38]. Participants’ permission will be obtained but they will not be identified in transcripts.

The economic analysis will involve both a cost analysis and cost-effectiveness analysis. This will be carried out from the perspective of the health services, including both Medicare and non- Medicare health costs, over a time horizon of 2 years. A cost analysis will provide information relating to set up, recruitment and program implementation of the RCT. While the analysis will provide specific cost details about running the RCT, the main interest will focus on the costs associated with future roll-out. Estimation will allow healthcare organisations to gauge the cost of conducting a similar program in the future.

The cost-effectiveness analysis of the trial intervention will involve the construction of a decision analytical model that captures data on both the cost and effectiveness of the intervention and non- intervention groups. The cost-effectiveness analysis will compare the difference in costs and effectiveness of the intervention and control groups, by calculating the incremental cost per Quality-Adjusted Life-Years gained by the intervention.

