## Methods

### Study design

This 6-month RCT will identify and recruit insufficiently active adults aged 50 to 69 with central obesity, residing in Albany, Western Australia, to participate in a home-based physical activity, nutrition, and healthy weight management intervention. Additional file 1: Figure S1 summarises the study design. A total of 500 participants with or at risk of metabolic syndrome will be recruited and randomised into intervention (n = 250) and wait-listed control (n = 250) groups. Data will be collected from both groups at baseline and 6 months to assess changes in outcome measures. Ethical approval of the study has been obtained from the Human Research Ethics Committee of Curtin University (HR149_2013). All participants will be informed of the research aims and objectives, and that confidentiality will be maintained throughout the study. Information and consent forms will be provided prior to entry into the RCT and participants will be free to withdraw from the program at any time.

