### Recruitment

Study participants aged 50–69 years and insufficiently active (less than 150 minutes of moderate physical activity per week) [11] will be recruited. Additional criteria for metabolic syndrome is based on assessing the following International Diabetes Federation (IDF) metabolic syndrome criteria [5]: central obesity (waist circumference >94 cm men or >80 cm women [Europids, Sub-Saharan Africans, Eastern Mediterranean, Middle East]; >90 cm men or >80 cm women [South Asians, Chinese, Japanese]); plus any two of: raised triglyceride level (>1.7 mM, or treatment for this); reduced HDL-cholesterol (<1.03 mM in males and <1.29 mM in females, or treatment for this); raised blood pressure (systolic ≥130 mmHg or diastolic ≥85 mmHg, or treatment of previously diagnosed hypertension); raised fasting plasma glucose (≥5.6 mM). However, only one instead of two of the latter four conditions needs to be satisfied to increase the potential pool of at risk participants. Identifying participants at risk of developing metabolic syndrome will enable appropriate intervention to be implemented, with the aim of preventing the onset of the syndrome and potential for type 2 diabetes and cardiovascular disease [12].

The following exclusion criteria will apply: previous diagnosis of diabetes mellitus (other than gestational diabetes); receiving treatment to lower blood glucose; on a weight loss diet or having weight fluctuations of >5% within the past 6 months; involvement in another physical activity and/or nutrition program; or a partner/individual residing in the same household as another participant already recruited for the study (to avoid contamination).

After the initial screening (n = 1000), it is expected that 625 participants will be eligible to join the study. Allowing for a subsequent 5% withdrawal rate and another 15% loss to follow-up, a final sample size of n = 250 intervention and n = 250 controls is anticipated, with quota sampling to ensure equal numbers of males and females. These figures are based on the pilot recruitment and data collection phase of the study.

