### Sample size

The power calculations are based on a logistic mixed regression model with the outcome variable being the prevalence of physical activity participation. Assuming 80% complete data across the assessments due to attrition and non-respondents, a total of n = 625 subjects satisfying the selection criteria will be initially recruited. In the power analyses, effect sizes of interest are associated with the time (pre-post) and intervention group parameters. For the mixed regression analysis, a final sample size of n = 500 [125 per gender by intervention condition] will provide sufficient power (80%) to detect a medium effect size at 5% significance level for the group by time interaction term accounting for gender but without other covariate adjustment.

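### Intention-to-treat is given only a sensitivity role and no main analysis set is named, although 20% of participants are expected to lack complete data

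*Protocol article*

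**What the plan says.** The Statistical analysis section of the protocol article gives the model: "Continuous and categorical outcomes will be analysed using generalised linear mixed regression models, accounting for the correlations between repeated measures and clustering of the observations". The next sentence is the article's only mention of intention-to-treat: "Intention-to-treat analysis will be conducted to assess sensitivity of the results to the expected attrition and withdrawal of participants from the RCT". No section says which participants enter the mixed models. Completers and non-completers are mentioned only under Process evaluation, for exit interviews.

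The expected loss appears twice. Recruitment has "Allowing for a subsequent 5% withdrawal rate and another 15% loss to follow-up", which leads to a final 250 per arm. Sample size has "Assuming 80% complete data across the assessments due to attrition and non-respondents, a total of n = 625 subjects", and then claims power on what remains: "a final sample size of n = 500 [125 per gender by intervention condition] will provide sufficient power (80%) to detect a medium effect size".

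Study design describes the same 500 differently. There, 500 participants "will be recruited and randomised into intervention (n = 250) and wait-listed control (n = 250) groups".

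**The concern.** In the intention-to-treat sentence, the results already exist and intention-to-treat tests how far attrition disturbs them. For a randomised trial this order is inverted. The comparison of all randomised participants in their assigned arms should carry the conclusion, and sensitivity analyses should vary what is assumed about the missing values. An analysis plan that followed the sentence literally would be free to take its headline estimate from another set.

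This matters because the expected loss is large and the design gives reasons for it to differ by arm. Controls receive the program only after their post-test data collection, which is an incentive to attend at 6 months. Intervention participants already hold the materials, and they are asked to set goals, track behaviour, wear an accelerometer and take five scheduled calls. The direction is not certain, since controls may also drift away while waiting. If those who leave do worse than those who stay, and the arms lose different numbers or different kinds of people, a comparison of those who stay no longer has the protection of randomisation.

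**Working it through.** **The plan's own figure.** Complete data needed: 500. Completeness assumed: 80%. 500 / 0.80 = 625, which matches Sample size. The split in Recruitment agrees: 5% + 15% = 20%, and 625 × 0.80 = 500. Applied in sequence, 625 × 0.95 × 0.85 = 504.7, close to 500. So 625 − 500 = 125 people are expected to lack complete data.

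**What a completer comparison could do, continuous outcome.** Let a be the attrition in an arm and δ the amount by which its drop-outs do worse than its completers. The mean of all randomised in that arm is the completer mean minus a × δ. The bias of the completer contrast is therefore

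bias = a_I × δ_I − a_C × δ_C,

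or δ × (a_I − a_C) when δ is the same in both arms. The article gives neither attrition by arm nor δ, so the values below are assumptions.

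| Attrition, intervention v control | δ (SD), both arms | Bias (SD) |
|---|---|---|
| 20% v 20% | any | 0 |
| any | 0 | 0 |
| 25% v 15% | 0.3 to 0.5 | 0.10 × δ = 0.03 to 0.05 |
| 30% v 10% (wider assumption) | 0.3 to 0.5 | 0.20 × δ = 0.06 to 0.10 |

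**The same on a binary outcome,** the type that the trial is powered on. Assume no true effect, 50% active in each arm and 312.5 randomised per arm.
- 25% v 15% attrition, 30% active among all drop-outs: observed (0.5 − 0.25 × 0.3) / 0.75 = 56.7% v (0.5 − 0.15 × 0.3) / 0.85 = 53.5%. The bias is 3.1 points, and the two-sided type I error is about 11% instead of 5%.
- 20% in both arms, but 30% active among intervention drop-outs and 50% among control drop-outs: (0.5 − 0.2 × 0.3) / 0.8 = 55% v 50%. The bias is 5 points, and the type I error is about 20%. Equal attrition rates are thus no protection if the arms lose different kinds of people.
- 20% in both arms with the same prognosis among drop-outs: bias 0, type I error 5%.

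**Does the planned mixed model remove this?** There are two assessments, baseline and 6 months. In a linear model with data missing at random, the likelihood estimate of an arm's 6-month mean is

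completer 6-month mean + β × (baseline mean of all − baseline mean of completers),

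where β is the slope of the 6-month value on baseline. If drop-out is unrelated to baseline, the bracket is zero in expectation and the estimate equals the completer estimate. The 0.03 to 0.05 SD then stays as it is. The model corrects only the part of drop-out that baseline predicts.

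**Who is in the intention-to-treat set.** On Recruitment and Sample size, about 625 are randomised (312 or 313 per arm) and 500 finish. On Study design, 500 are randomised, and 80% completeness would leave 500 × 0.80 = 400. Both cannot be the denominator.

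**The case against.** A reader might infer that the main result rests on a comparison of completers. The article does not support this. No section applies the words completer, complete-case or per-protocol to the main analysis. Inflating 500 to 625 so that enough people have outcome data is equally routine in trials analysed by intention-to-treat. The planned mixed model can keep participants with baseline data only in their assigned arm. The sentence might also have been meant to say that an intention-to-treat analysis, for example with imputation, is how attrition will be handled. All of this stands.

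It can also be said that analysis sets are commonly left to a statistical analysis plan, which is not shown. Silence alone would indeed be no finding. Here, however, the article does speak: it gives intention-to-treat a role, and that role is the wrong one.

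The strongest objection is that naming all randomised participants as the primary set would not by itself change the estimate much. As the working shows, with two assessments and drop-out unrelated to baseline, the mixed model returns the completer answer. This also stands. The bias figures measure what outcome-related missing data could do, not the cost of the sentence alone.

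**Conclusion.** The point holds as a misassigned role for intention-to-treat together with an unnamed main analysis set, against a stated 20% expectation of incomplete data. It does not establish that the trial will be analysed on completers.

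The possible bias runs from zero upwards. The figure of 0.03 to 0.05 SD needs three assumptions that the article does not supply: a completer-type comparison, 25% v 15% attrition, and drop-outs 0.3 to 0.5 SD worse. A reader might also infer that the effect would be overstated by 25% (1 / 0.8). That needs 20% loss in the intervention arm and drop-outs who gain nothing. It would be the same under a missing-at-random mixed model when drop-out is unrelated to baseline, so it cannot be charged to the wording.

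The correction is still worth making before outcome data are analysed. It fixes which comparison the conclusion rests on and directs the sensitivity analyses at the real source of risk. The conflict between 500 and 625 randomised is separate from these assumptions and is evident from the text.

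**What to change.** - State that the primary analysis includes all randomised participants in their assigned arm, using every available baseline and 6-month value in the mixed model already planned, and that it assumes data missing at random.
- Label any completer analysis as supportive.
- Replace the sentence that gives intention-to-treat a sensitivity role with sensitivity analyses that vary the missing-data assumption: delta-adjusted imputation over a prespecified range (on the log-odds scale for binary outcomes), or control-based imputation for intervention drop-outs.
- Where consent allows, invite those who stop the program to attend the 6-month measurement. This reduces the missing data instead of modelling them.
- Reconcile Study design (500 recruited and randomised) with Recruitment and Sample size (625 initially, 500 final), so that the intention-to-treat denominator is fixed.

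The cost is a few sentences, modest programming and some follow-up effort. The sensitivity estimates may be less favourable to the intervention than the primary one.

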### Sample size

The power calculations are based on a logistic mixed regression model with the outcome variable being the prevalence of physical activity participation. Assuming 80% complete data across the assessments due to attrition and non-respondents, a total of n = 625 subjects satisfying the selection criteria will be initially recruited. In the power analyses, effect sizes of interest are associated with the time (pre-post) and intervention group parameters. For the mixed regression analysis, a final sample size of n = 500 [125 per gender by intervention condition] will provide sufficient power (80%) to detect a medium effect size at 5% significance level for the group by time interaction term accounting for gender but without other covariate adjustment.

## Discussion

### Results of the APAN study are due in late 2015

It is imperative to target middle-aged (50–69 years old) adults to address the increasing prevalence of overweight/obesity and chronic disease in Australia’s ageing population [2]. Identifying those at risk of metabolic syndrome, who are at high risk of type 2 diabetes mellitus and cardiovascular disease, can potentially lead to reduced prevalence and delayed onset of these diseases [8,39]. Providing home-based interventions for middle-aged adults still in the workforce allows for greater engagement of this group through flexibility. Flexibility provided by home-based interventions for middle-aged adults still engaged in the workforce should potentially lead to greater engagement of this hard to reach group.

Developing cost-effective strategies for identifying and managing individuals with overweight/obesity and metabolic syndrome via screening will have implications for primary care, by providing a window of opportunity for early intervention [40]. This community-based intervention will also enable large scale field testing in a rural setting, an area where little research has been conducted. Strategies evaluated as being successful and appropriate can be rolled out in other rural communities.

Cost-benefit analysis will be performed to determine the potential reduction in future chronic disease-related health costs, providing recommendations for policy and planning actions relating to the control of overweight/obesity, metabolic syndrome screening and intervention. The outcomes of the project will have potentially significant benefits to the Australian community through reduced chronic disease prevalence and improved quality of life. It will also likely have relevance to similar communities internationally.

## Abbreviations

RCT: Randomised controlled trial
BMI: Body mass index
HDL: High-density lipoprotein
APAN: Albany physical activity and nutrition
PALS: Perth active living seniors
PANS: Physical activity and nutrition for seniors
LDL: Low-density lipoprotein
